**4. Intervention Methods**

The intervention will be administered five times weekly over a four-week period.

**4.1 iTBS Intervention Protocol**

Before each robot-assisted training session begins, TBS intervention will be administered using the Wuhan Yiruide paired transcranial magnetic therapy instrument (Model: N50000) and its matching double-cone coil. Stimulation will target the "hotspot" within the lower limb motor cortex M1 area. This location will be determined by identifying the position that produces the maximum motor evoked potential (MEP) amplitude in the tibialis anterior muscle, supplemented by resting motor threshold (rMT) testing.

The intervention protocol will consist of two consecutive segments: priming (using cTBS) followed by activation (iTBS). The cTBS phase will deliver 600 pulses in approximately 40 seconds, using 200 sets of continuous stimulus trains, with a pulse frequency of 50Hz and a repetition frequency of 5Hz. The iTBS phase will then be implemented: sending 2-second pulse trains of 3 pulses at 50Hz frequency, followed by an 8-second rest period. This 10-second cycle is repeated 20 times, totaling 600 pulses sent in approximately 192 seconds. All stimulation intensities are set to 80% of the individual active motor threshold (aMT). This threshold is defined as the minimum intensity required to elicit MEPs with peak-to-peak amplitude exceeding 200μV in the tibialis anterior muscle in at least 5 out of 10 trials.

For sham stimulation, the same double-cone coil as used for active stimulation will be employed. This coil will be configured for special sham stimulation mode, simulating the audible "click" sound produced by active TMS without delivering a clinically significant magnetic field to the scalp. The coil will be placed in the exact same scalp position and at the same angle as during active stimulation, using the same fixation bracket to ensure consistent positioning and implementation of blinding.

**4.2 Robot-Assisted Training Intervention Protocol**

All patients will receive a standardized robot-assisted training program using the REX self-balancing exoskeleton rehabilitation robot (Rex Bionics Ltd., New Zealand). All robot-assisted training will be conducted after the TBS intervention, and the training interval should be as short as possible (less than 15 minutes). The daily 30-minute training consists of three separate 10-minute programs:

Program 1: Standing Activity Training: This session focuses on improving trunk control ability and upper-lower limb coordination during stable standing, trained through tasks such as targeted reaching.

Program 2: Elastic Band Resistance Training: Utilizing Proprioceptive Neuromuscular Facilitation (PNF) patterns, aiming to promote extension function of the affected lower limb, enhancing muscle strength and coordination.

Program 3: Lower Limb Functional Training: Through exercises such as single-leg weight bearing, lateral stepping, and deep squats, to improve functional strength, balance ability, and mobility.

All robot-assisted training is supervised throughout by experienced physical therapists. The therapist dynamically adjusts the robot assistance intensity and training difficulty based on the patient's real-time performance and tolerance, while providing immediate verbal feedback.

**5. Evaluation Indicators**

Assessments are conducted at the following time points: pre-intervention (T0), post-intervention at 2 weeks (T1), 4 weeks (T2), and 6-week follow-up (T3). The assessors are not involved in the research process. These assessors have over 5 years of clinical experience and are proficient in the application of assessment tools and methods. Assessors are blinded to group assignment.

**5.1 Primary Outcome Measure**

Fugl-Meyer Assessment for Lower Extremity (FMA-LE): Used to quantitatively assess the impairment and recovery of lower limb motor function in stroke patients, systematically evaluating dimensions such as reflexes, synergistic movements, and coordination. This scale uses a 3-level ordinal score (0=severe dysfunction, 1=partial dysfunction, 2=no dysfunction), with a total score of 34 points. It has good reliability and validity and is a widely recognized clinical tool for assessing lower limb motor function.

**5.2 Secondary Outcome Measures**

(1) Postural Assessment Scale for Stroke (PASS): A postural control assessment tool specifically designed for stroke patients, containing 12 items covering static posture maintenance, dynamic center of gravity transfer, body position changes, and anti-interference ability. Each item is scored from 0-3 based on the patient's ability to complete it, with a higher total score indicating better postural control ability.

(2) Modified Barthel Index (MBI): The Barthel Index assesses patients' activities of daily living, including feeding, bathing, grooming, dressing, bowel and bladder control, toileting, bed-chair transfer, walking on level ground, and ascending/descending stairs. The total score is 100 points, with a higher score indicating better ability in activities of daily living.

**5.3 Neurophysiological and Biomechanical Indicators**

(1) Functional Near-Infrared Spectroscopy (fNIRS):

- Device: NirSmart-3000B fNIRS system (Danyang Huichuang Medical Equipment Co., Ltd.)
- Parameters: 16 light sources, 18 detectors (40 effective channels total), dual wavelength (730nm & 850nm), sampling frequency 11Hz
- Procedure: Before data acquisition, patients rest in a quiet, relaxed state for about 1 minute to ensure hemodynamic baseline stability, followed by an 8-minute resting-state fNIRS scan, during which they remain awake and still.
- Analysis Indicators: Primarily analyze changes in oxygenated hemoglobin and deoxygenated hemoglobin concentrations in various brain regions, and assess the functional integration of motor-related cortical networks through the amplitude of low-frequency fluctuations and functional connectivity analysis based on HbO₂ signals.

(2) Electroencephalography (EEG):

- Device: GES 400 high-density 64-channel EEG system (EGI, USA)
- Parameters: Electrodes arranged according to the International 10-20 system, referenced to Cz, sampling rate ≥8 kHz/channel, input noise ≤1μV
- Procedure: Before acquisition, patients rest quietly for 1 minute, followed by a 5-minute closed-eye resting-state EEG recording.
- Analysis Indicators: After signal preprocessing using EEGLAB toolbox, focus on the absolute power values in the alpha frequency band for brain regions related to motor function (electrode sites C3, C4, FC1, FC2, FCz, FC3, FC4).

(3) Three-Dimensional Gait Analysis:

- Device: Qualisys three-dimensional motion capture system
- Technology: Built-in 3D motion sensor adaptive technology, automatically tracking step frequency and gait through computer learning algorithms, precisely detecting multi-dimensional angle changes.
- Analysis Indicators: Automatically collect and analyze basic gait parameters (step frequency, step time, stride length, etc.), and record usage data after a single startup.

(4) Surface Electromyography (sEMG):

- Device: DELSYS Trigno™ wireless biofeedback system (USA)
- Tested Muscles: Rectus femoris, biceps femoris, tibialis anterior, gastrocnemius.
- Analysis Indicators: Root Mean Square value (reflects the overall level of muscle electrical activity in a specific period, related to motor unit recruitment and synchronization of muscle fiber discharge); Median Frequency (the frequency value that divides the EMG signal power spectrum area in half. It reflects the median level of muscle fiber discharge rate, commonly used to assess local muscle fatigue and the mobilization of different types of muscle fibers).

(5) Motor Evoked Potentials (MEP):

- Device: Wuhan Yiruide Transcranial Magnetic Therapy Instrument (N50000) and matching double-cone coil (VCZ001)
- Electrode Placement: According to SENIAM guidelines, recording electrode placed on the belly of the tibialis anterior muscle, reference electrode on the medial malleolus, ground electrode on the contralateral limb.
- Measurement Parameters:
  - Resting Motor Threshold (rMT): The minimum stimulation intensity required to elicit MEPs with peak amplitude ≥50 μV in the relaxed TA muscle in at least 5 out of 10 consecutive stimulations.
  - Active Motor Threshold (aMT): The minimum stimulation intensity required to elicit MEPs with peak amplitude ≥200 μV in the slightly voluntarily contracted TA muscle (about 20% maximum voluntary contraction) in at least 5 out of 10 consecutive stimulations.
  - Basic MEP Parameters: Obtain at least 15 valid MEPs at 130% rMT intensity, record amplitude and latency.
  - Recruitment Curve: Stimulation intensity increases from 80% rMT to 150% rMT, 5 stimuli given at each 10% intensity level, analyze parameters such as RC slope.

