**1.1 Inclusion Criteria**

(1) Stroke diagnosed by CT or MRI.

(2) Age 40-80 years old.

(3) Stable condition, first onset of illness, duration 1-3 months.

(4) Able to walk independently or with assistance for more than 10m, Brunnstrom stage III-V lower limb.

(5) Cognitive clarity, ability to follow simple verbal commands or instructions, MoCA≥26.

(6) Informed consent signed by the patient or his/her relatives.

(7) No history of epilepsy.

(8) No contraindications to TMS examination.

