**2. Sample Size Estimation**

Assuming the endpoint FMA-LE scale value in the preconditioned iTBS group is 3 points higher than in the non-preconditioned iTBS group, and the combined standard deviation for all groups is 2.5 points. Based on existing research results and clinical experience, at a statistical significance level of α=0.05, to achieve 90% statistical power, and considering a 20% follow-up loss rate, calculation using PASS 15 software indicates: at least 20 patients are needed per group, totaling 60 patients.

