**3. Random Grouping**

A total of 60 eligible stroke patients will be enrolled in this study. Following the baseline assessment, a computer-generated randomization sequence will be used to assign all participants in a 1:1:1 ratio to one of three parallel intervention groups: the priming iTBS group (n=20), the non-priming iTBS group (n=20), or the sham stimulation group (n=20). The allocation sequence will be concealed from the researchers enrolling participants. After a participant provides informed consent and all baseline assessments (T0) are completed, the research coordinator will access the central web-based system. The system will then reveal the group allocation only to the unblinded physical therapist responsible for administering the intervention. This ensures that outcome assessors and participants remain blinded.

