**6. Statistical Analysis**

SPSS 22.0 software will be used. Demographic and baseline characteristics will be compared using one-way analysis of variance (ANOVA) or Fisher's exact test. Mixed-design ANOVA (between-subjects factor: group; within-subjects factor: time) and the interaction between time and group will be analyzed to compare dependent outcomes across groups at the three time points (T0-T0, T1-T0, and T2-T0). The significance level is set at P < 0.05. If any significant time-by-group interaction effects are found, pairwise t-tests will be used for comparisons, comparing baseline changes with a Bonferroni correction threshold of 0.017. If any significant time-by-group interaction effects are found, exploratory subgroup analyses will be conducted to investigate potential differential effects among different functional groups. Due to the exploratory nature of the study, we applied the Bonferroni correction only in the post-hoc comparisons of the primary outcome (P=0.017, number of comparisons=3).

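### EEG alpha power is defined at left and right scalp sites with no rule for lesion side, so any lateralised effect is diluted at the six lateral electrodes if analysed as written

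*Protocol*

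**What the plan says.** - **EEG indicator (Protocol 5.3, item 2).** After preprocessing, the analysis will "focus on the absolute power values in the alpha frequency band for brain regions related to motor function", and the sites are listed as "electrode sites C3, C4, FC1, FC2, FCz, FC3, FC4". C3, FC1 and FC3 are on the left, C4, FC2 and FC4 on the right, and FCz on the midline.
- **Eligibility (1.1 and 1.2).** Entry requires "Stroke diagnosed by CT or MRI" and a first onset. Neither list limits the lesion to one hemisphere or excludes bilateral or midline lesions.
- **Randomisation (3).** The sequence will "assign all participants in a 1:1:1 ratio to one of three parallel intervention groups". No stratification by lesion side is stated.
- **Model (6).** Outcomes are compared as changes from T0 by "Mixed-design ANOVA (between-subjects factor: group; within-subjects factor: time"). Neither hemisphere nor lesion side is a factor.
- **Stimulation (4.1).** The target is the leg hotspot in M1. The section does not say whether this is in the lesioned or the intact hemisphere.

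Nothing in the protocol recodes electrodes by lesion side, and nothing forbids it.

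**The concern.** In a stroke trial the natural unit for a cortical measure is the lesioned or the intact hemisphere. The protocol instead names the units by scalp side. C3 overlies the lesioned hemisphere in a patient with a left-sided stroke and the intact hemisphere in a patient with a right-sided one. A group mean at C3 then mixes the two. This mixing arises across patients at a single electrode, so it does not depend on any rule for pooling electrodes.

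If the treatment changes alpha power equally in both hemispheres, nothing is lost. If the change differs between hemispheres, each lateral site shows a blend, and patients within an arm also become more variable. What is at stake is the sensitivity of the EEG indicator to a lateralised effect.

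**Working it through.** **The plan's own figure.** The only design calculation is for FMA-LE (section 2): the preconditioned group "is 3 points higher than in the non-preconditioned iTBS group", SD 2.5, α 0.05, power 90%, 20% loss. The standardised difference is 3/2.5 = 1.2. A two-sided two-sample t-test needs 16 per group (power 90.7%), and 16/0.8 = 20, which reproduces the stated 20 per group. No effect size, SD or lesion split is given for EEG, so what follows is an illustration.

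**Assumptions (not in the documents).**
- d is the ipsilesional effect in SD units; the contralesional effect is r·d.
- p is the share of left-sided lesions, with every lesion on one side.
- The control arm has no effect and SD 1.
- 16 patients per arm are evaluable (20 × 0.8), with a two-sided α of 0.05.

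**Share of the effect kept.**
- At left sites: p + (1−p)·r
- At right sites: (1−p) + p·r
- At p = 0.5 both equal (1+r)/2.

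**Standardised effect at a left site.** Mixing adds p(1−p)·d²(1−r)² to the treated-arm variance. Averaged over the two arms, the variance is 1 + p(1−p)·d²(1−r)²/2, so

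d* = d·[p + (1−p)r] / √(1 + p(1−p)·d²(1−r)²/2)

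**Worked case:** d = 1.0, r = 0, p = 0.5. d* = 0.5/√(1 + 0.25/2) = 0.5/√1.125 = 0.47.

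**Results at p = 0.5** (power from the noncentral t):

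| r | Share kept | d*, d = 1.0 | Power, d = 1.0 | Power, d = 1.2 |
|---|---|---|---|---|
| 1 (bilateral) | 100% | 1.00 | 78% | 91% |
| 0.5 | 75% | 0.74 | 53% | 67% |
| 0 (ipsilesional only) | 50% | 0.47 | 25% | 33% |
| −0.5 | 25% | 0.22 | 9% | 11% |
| −1 (equal and opposite) | 0% | 0 | 5% | 5% |

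With sites aligned to the lesion, power at the ipsilesional site is 78% (d = 1.0) or 91% (d = 1.2) in every row. The value d = 1.2 is borrowed from FMA-LE only to show a second point.

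**Unequal split:** d = 1.0, r = 0, p = 0.7. The left sites keep 70%: d* = 0.7/√(1 + 0.21/2) = 0.67, power about 45%. The right sites keep 30%: d* = 0.3/√1.105 = 0.29, power about 12%.

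**FCz** has no left or right counterpart, so this mixing does not arise there.

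**The case against.** **It may be settled in an analysis plan that is not shown.** Electrodes carry 10-20 labels whatever coding follows. The list contains both members of each pair, which is what recoding needs, and mirroring is a derivation step that a protocol can leave to the SAP. This stands in part: the protocol does not rule recoding out, so the point is conditional on analysis as written. But the protocol names the units and the model factors, and an SAP that followed them literally would reproduce the mixing.

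**Stronger readings that a reader might infer, and that the documents do not support:**
- *That the EEG effect is largely lost.* The share kept runs from 0% to 100%, depending on an effect ratio and a lesion split that the documents do not give. A bilateral effect loses nothing.
- *That the EEG cannot inform on mechanism.* FCz is unaffected, and the protocol states no specifically lateralised EEG hypothesis. Sensitivity is reduced only for a lateralised effect.
- *That chance imbalance in lesion side biases the group comparison.* Allocation is randomised and the analysis uses change from T0. Imbalance adds noise, which the test's error rate already covers.
- *That the fNIRS analysis has the same defect.* Section 5.3 speaks of brain regions for fNIRS and names no left or right channels, so there is no fixed-side definition to correct.

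**The consequence is small.** EEG is listed apart from the primary and secondary outcomes, and section 6 calls the study exploratory. This stands and limits the weight of the point.

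**Conclusion.** The point holds in a limited form. Sites fixed by scalp side, unrestricted lesion side and a model with only group and time together mean that, analysed as written, an effect that differs between hemispheres is diluted at six of the seven EEG sites.

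The amount cannot be determined from the documents. The figure of 0.47, with power of about 25% against 78%, holds only for an ipsilesional-only effect of 1.0 SD, a 50:50 lesion split and 16 evaluable patients per arm. It is not an estimate for this trial. The matter is a low-cost improvement to an exploratory indicator.

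**What to change.** Before analysis, add to section 5.3 or to the SAP:

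1. Take lesion side from the qualifying CT or MRI and mirror the EEG data for one lesion side.
2. Define the lateral sites as ipsilesional and contralesional members of the pairs C3/C4, FC1/FC2 and FC3/FC4, with FCz as midline.
3. Analyse change from T0 on these aligned sites.
4. Set a rule in advance for bilateral or midline lesions, which have no single side to align to: for example, analysis at FCz only, or exclusion from the lateral-site analysis.

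Section 4.1 should also state which hemisphere is stimulated, so that the aligned results can be interpreted.

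The cost is a few sentences and a relabelling step in preprocessing; data collection does not change. The one small downside is that any patients covered by item 4 drop out of the lateral-site analysis.

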**6. Statistical Analysis**

SPSS 22.0 software will be used. Demographic and baseline characteristics will be compared using one-way analysis of variance (ANOVA) or Fisher's exact test. Mixed-design ANOVA (between-subjects factor: group; within-subjects factor: time) and the interaction between time and group will be analyzed to compare dependent outcomes across groups at the three time points (T0-T0, T1-T0, and T2-T0). The significance level is set at P < 0.05. If any significant time-by-group interaction effects are found, pairwise t-tests will be used for comparisons, comparing baseline changes with a Bonferroni correction threshold of 0.017. If any significant time-by-group interaction effects are found, exploratory subgroup analyses will be conducted to investigate potential differential effects among different functional groups. Due to the exploratory nature of the study, we applied the Bonferroni correction only in the post-hoc comparisons of the primary outcome (P=0.017, number of comparisons=3).

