**7. Safety Monitoring and Adverse Event Handling**

**7.1 Safety Monitoring**

**7.1.1 Monitoring Entities and Responsibilities**

- Safety Supervisor: Must hold a valid clinical physician license and have ≥3 years of clinical experience, responsible for monitoring the safety of the intervention process, focusing on risks related to TMS and robot-assisted training, and leading adverse event management.
- Physical Therapist: When performing TMS interventions and robot-assisted training, assess the patient's mental state, fatigue, pain, blood pressure, heart rate, and muscle tone in the affected limb before intervention using scales such as Borg CR10, VAS, Modified Ashworth Scale (MAS); during intervention, inquire about the patient's feelings every 10 minutes, monitor heart rate and respiration, have a blood pressure monitor and pulse oximeter ready; after intervention, record patient reactions.
- Rehabilitation Assessor: Assessments using fNIRS, three-dimensional gait analysis, EEG, sEMG, and MEP were conducted at three time points: baseline (T0), 2-week mid-intervention (T1), and immediately post-intervention at 4 weeks (T2). The FMA-LE and MBI were administered at T0, T1, T2, and at the 6-week follow-up (T3). Safety was evaluated by monitoring changes in all collected data, with any anomalies promptly reported to the safety monitor.

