**7.3 Patient Withdrawal Handling**

Perform unblinding for withdrawn patients; make every effort to collect the patient's last medical assessment data and basic information; inform the patient that necessary medical consultation and support are still available after withdrawal.

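### The mixed-design ANOVA leaves out any patient who misses T1 or T2, so with the planned 20% loss up to 12 of 60 randomised patients would drop out of the primary test and their observed data would go unused.

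*Protocol*

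**What the plan says.** Protocol Section 6 names the software ("SPSS 22.0 software will be used") and the method: "Mixed-design ANOVA (between-subjects factor: group; within-subjects factor: time) and the interaction between time and group will be analyzed". The visits entering it are given as "compare dependent outcomes across groups at the three time points (T0-T0, T1-T0, and T2-T0", that is T0, T1 and T2. If the interaction is significant, pairwise t-tests on change from baseline follow, at a threshold of 0.017.

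Section 7.1.1 shows that the primary outcome is also measured later: "The FMA-LE and MBI were administered at T0, T1, T2, and at the 6-week follow-up (T3". T3 is therefore outside the ANOVA.

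Section 2 sets the sample size "considering a 20% follow-up loss rate" and arrives at 20 per group. Section 7.3 tells staff to "make every effort to collect" the last assessment of a patient who withdraws, but no section says how that assessment enters the analysis. The protocol names no analysis set, no imputation and no model that keeps incomplete records.

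**The concern.** A split-plot ANOVA works on a complete row per patient. A patient seen at T0 and T1 but not at T2 contributes nothing to the group-by-time test, although two of the three values exist. This follows from the method that Section 6 chooses. It is not a complaint that a missing-data section is absent.

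Two things are at stake. First, data that the trial takes trouble to collect are not used. Second, patients who complete need not be comparable across arms in the way randomised patients are. The regimen is five sessions a week for four weeks, 20 in all. Section 4.1 describes a sham mode without a clinically significant magnetic field, and Section 7.2.2 lists events such as local pain, dizziness and hearing problems that lead to reducing, suspending or stopping the intervention. Loss could therefore differ in rate or cause between active and sham arms. If it also tracks early response, the completers' difference is shifted.

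**Working it through.** **Inputs from the protocol.** Difference 3 points ("Assuming the endpoint FMA-LE scale value in the preconditioned iTBS group is 3 points higher than in the non-preconditioned iTBS group"); SD 2.5 ("the combined standard deviation for all groups is 2.5 points"); α 0.05, power 90%, loss 20% (Section 2); 20 per group, three groups (Section 3); pairwise threshold 0.017 (Section 6). Sidedness is not stated; two-sided is assumed.

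**Step 1: reproduce the plan's sample size.** For a two-sample t-test with n per group, the noncentrality is Δ / (SD × √(2/n)) on 2n − 2 degrees of freedom.
- n = 16: 3 / (2.5 × √(2/16)) = 3 / 0.884 = 3.39 on 30 df. Power is 90.7% at 0.05. With n = 15 it is 88.7%, so 16 is the smallest n that reaches 90%.
- Inflation: 16 / (1 − 0.20) = 20 per group, 60 in total. This matches Section 2.

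The design therefore already counts on about 16 analysed patients per group, and the loss costs no planned power at 0.05. At the 0.017 threshold, 16 per group gives 80.1%; that is a separate matter from this point.

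**Step 2: how many patients leave.** 60 × 0.20 = 12, leaving 48 (16 per group). This is a ceiling. Section 2 attaches no time to the loss, and a patient lost only after T2 stays in the ANOVA.

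**Step 3: who leaves which test.**

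| Patient | Group-by-time ANOVA | T1−T0 t-test | T2−T0 t-test |
|---|---|---|---|
| Missing T1 only | out | out | in |
| Lost after T1 | out | in | out |
| Lost before T1 | out | out | out |
| Lost after T2 | in | in | in |

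The t-test columns assume that each test uses every patient who has both values.

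**Step 4: size of a possible bias.** The documents give no correlation between visits and no dropout mechanism, so these are assumptions. The comparison estimator predicts missing T2 values from T0 and T1 within arm. It stands in for a likelihood-based model that uses all observed visits.

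(a) Two arms, no true difference, SD 2.5, between-visit correlation 0.7, loss after T1 partly driven by the T0-to-T1 change, 400,000 simulated patients per arm:

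| Loss in arm A / arm B | Completers' difference in T2−T0 | Using T0 and T1 |
|---|---|---|
| random 20% / random 20% | 0.0 | 0.0 |
| poor responders 20% / poor responders 20% | 0.01 | 0.01 |
| poor responders 20% / random 20% | 0.24 | 0.0 |
| poor responders 30% / poor responders 10% | 0.21 | 0.0 |
| poor responders 20% / good responders 20% | 0.48 | 0.0 |

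(b) 20 per arm, true difference 3 at T2 and 1.5 at T1, SD 2.5, correlation 0.5 to 0.7, 4 of 20 lost after T1, with poor early responders lost in the priming arm and random loss in the comparator, 4,000 replicates per setting. The completers' difference averages 3.09 to 3.39, depending on how closely loss follows early response. The estimator using T0 and T1 averages 2.98 to 3.02. With the same mechanism in both arms, the completers' difference is again about 3.0.

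The overstatement in (b) is thus about 0.1 to 0.4 points, or 3% to 13% of the planned 3 points (0.09/3 to 0.39/3).

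**The case against.** The strongest reply is that the protocol never restricts the analysis to completers, that imputation and analysis sets are often left to a statistical analysis plan, and that an imputed data set can go through a mixed-design ANOVA. This is fair as to certainty: the exclusion follows from the named method and is not declared. But nothing in the protocol overrides it, and the method is fixed there.

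A reader might infer three stronger things that the documents do not support.

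- *Only patients complete at every visit are analysed, and the planned 20% loss makes this certain.* T3 is not in the ANOVA, so 12 of 60 is a maximum. Participants are inpatients on a four-week course, and some of the loss may fall after T2.
- *Everything an incomplete patient contributed is discarded.* That holds for the group-by-time test. The follow-up t-tests need only T0 and the visit compared, so part of such a patient's data can still enter there, as the table under step 3 shows.
- *A mixed model removes dropout bias of any size.* Suppose patients lost from one arm would have done 1.5 to 3 points worse. The completers' bias is then 0.2 × 1.5 = 0.3 to 0.2 × 3 = 0.6 points. If T0 and T1 do not predict that gap, the mixed model is biased as well. This figure has no source in the documents and is not a cost of the ANOVA alone.

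It is also fair that the bias is small beside the sampling error. With 16 per arm the standard error of a difference is 2.5 × √(2/16) = 0.88. For change scores at correlation 0.7 the SD is 2.5 × √(2 × 0.3) = 1.94 and the standard error 1.94 × √(2/16) = 0.68. A shift of 0.1 to 0.4 is well below either. That argues for calling the bias modest. It is no reason to keep a method that leaves observed data unused when a better one is available in the same software.

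**Conclusion.** The point holds in limited form. The ANOVA in Section 6 excludes from the group-by-time test any patient missing T1 or T2, and the change-score t-tests exclude anyone missing the visit compared. Up to 12 of 60 randomised patients are affected if all the planned loss occurs by T2. Planned power at 0.05 is unharmed. The cost is unused T0/T1 data and a conditional selection bias: about 0 if loss is random or has the same cause and rate in all arms, and roughly 0.1 to 0.4 FMA-LE points if loss follows early response in one arm only. The bias figures rest on the assumed correlations and dropout mechanisms in step 4; the documents neither support nor exclude them. The change should be made, but the finding does not by itself invalidate the trial.

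**What to change.** In Section 6, replace the mixed-design ANOVA and the change-score t-tests with a linear mixed model for repeated measures (SPSS MIXED, REML, unstructured covariance), fitted to all randomised patients as allocated and using all observed visits.

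Choose one of two ways to handle baseline and state it:
- Enter T0 as a response with a common mean across arms, so that patients lost before T1 stay in the model.
- Use T0 as a covariate with post-baseline visits as outcomes, and say that patients lost before T1 contribute no outcome.

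Take the three pairwise group contrasts at T2 from this model at the 0.017 threshold. The model is valid only if dropout depends on observed data, so add a simple sensitivity analysis for dropout that does not, for example a delta shift applied to the missing T2 values.

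The cost is new wording in Section 6, a different procedure in the same software and slightly more analysis work. No new data are needed. The price in assumptions is reliance on data missing at random, which the sensitivity analysis probes. The change should be fixed before unblinded data are seen, so that nobody later has to choose between a completers' and an all-data result.

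### The primary outcome is measured at the 6-week follow-up (T3), but section 6 fixes an analysis that ends at T2, so the T3 data have no planned efficacy analysis

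*Protocol*

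**What the plan says.** Section 5 lists four assessments: "pre-intervention (T0), post-intervention at 2 weeks (T1), 4 weeks (T2), and 6-week follow-up (T3". It does not say which measures are taken at which visit.

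Section 7.1.1 is more specific. The neurophysiological and biomechanical measures (fNIRS, gait, EEG, sEMG, MEP) are "conducted at three time points: baseline (T0), 2-week mid-intervention (T1), and immediately post-intervention at 4 weeks (T2". For the clinical scales it says "The FMA-LE and MBI were administered at T0, T1, T2, and at the 6-week follow-up (T3". FMA-LE is the sole primary outcome in section 5.1. PASS, a secondary outcome in section 5.2, appears in neither list of section 7.1.1.

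Section 6 prescribes a "Mixed-design ANOVA (between-subjects factor: group; within-subjects factor: time", used to "compare dependent outcomes across groups at the three time points (T0-T0, T1-T0, and T2-T0". Pairwise t-tests follow only if the time-by-group interaction is significant, "comparing baseline changes with a Bonferroni correction threshold of 0.017". No T3-T0 comparison appears. The only use that the protocol gives to data from T3 is the general statement in section 7.1.1 that changes in all collected data are watched for safety.

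No section names a primary time point for FMA-LE. The sample size in section 2 refers only to the endpoint value.

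**The concern.** Section 6 is not silent on time points. It gives their number and lists them, and the list conflicts with the schedule of the primary outcome. A statistician who follows section 6 leaves T3 out; one who analyses T3 departs from the protocol.

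At stake is the question that a follow-up visit normally serves, namely whether a benefit of priming outlasts the four weeks of treatment. With T3 measured but outside the plan, and no primary time point named, the choice to report or omit T3, and the weight given to it, could be made after the results are seen.

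**Working it through.** **1. Schedule against analysis**

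| Measure | Scheduled (sections 5, 7.1.1) | Analysed (section 6) |
|---|---|---|
| FMA-LE (primary), MBI | T0, T1, T2, T3 | T0, T1, T2 |
| fNIRS, gait, EEG, sEMG, MEP | T0, T1, T2 in 7.1.1; section 5 makes no distinction | T0, T1, T2 |
| PASS | T0 to T3 by section 5 in general terms; not listed in 7.1.1 | T0, T1, T2 |

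The analysis matches the schedule only in the second row.

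**2. Inputs**

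From section 2: difference 3, SD 2.5, α = 0.05 (two-sided assumed), power 90%, loss 20%. The standardised difference is 3/2.5 = 1.2. A two-sample t-test needs 15.6, so 16 per group, and 16/0.8 = 20. The stated 20 per group is reproduced, with 16 evaluable per group. The correlation ρ between visits is not in the protocol. It is assumed to be 0.6, equal for all pairs of visits, and varied in step 3.

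**3. An effect present only at T3**

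Let one of the three groups gain 3 points at T3 and nothing earlier.

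- *Stated test (T0, T1, T2).* The groups do not differ at any analysed visit, so the rejection rate is the false-positive rate of 5% for any ρ. Simulation (4,000 runs): 4.6%.
- *With T3 (four levels).* The sum of squared interaction effects is 3² × [(2/3)² + (1/3)² + (1/3)²] × [(3/4)² + 3 × (1/4)²] = 9 × 0.667 × 0.75 = 4.5. The noncentrality is λ = 16 × 4.5 / [2.5² × (1 − ρ)] = 11.52/(1 − ρ), on (2 × 3, 45 × 3) = (6, 135) degrees of freedom.

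| Assumed ρ | λ | Power with T3 included |
|---|---|---|
| 0.4 | 19.2 | 92% |
| 0.6 | 28.8 | 99% (simulation 98.95%) |
| 0.8 | 57.6 | above 99.9% |

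**4. Persisting against fading benefit**

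Let the gain be 1.5 points at T1 and 3 at T2. At T3 it either stays at 3 or returns to 0. By simulation the stated test rejects in 94.2% of trials when the gain persists and 94.5% when it is lost, which is the same result up to simulation error. With T3 in the model the overall interaction test rejects in 98.4% and 98.0%. The overall test therefore does not separate the two cases either; that takes the group comparison of T3-T0.

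**5. What T0-T0 does**

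It is zero for every patient. Two identities show the consequence.

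- *Interaction.* Subtracting a patient's own T0 from all of that patient's levels leaves every within-patient deviation unchanged. In one simulated data set with 20 per group, F was 6.552 on (4, 114) degrees of freedom for both raw scores and changes.
- *Group main effect of change.* (0 + d1 + d2)/3 = (2/3) × (d1 + d2)/2. Effect and error shrink by the same factor, so F is unchanged: 8.647 with and without the zero level in the same data.

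**6. What dropping the baseline level would do**

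Let one group gain a constant 3 points from T1 onward.

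- *As written (T0, T1, T2).* The sum of squares is 9 × 0.667 × [(2/3)² + 2 × (1/3)²] = 4.0. At ρ = 0.6, λ = 16 × 4.0/2.5 = 25.6 on (4, 90) degrees of freedom, and power is about 99%.
- *Baseline kept, T3 added.* Sum 4.5, λ = 28.8, about 99%.
- *Only T1-T0, T2-T0 and T3-T0.* The group profiles are parallel, the interaction is zero, λ = 0, and power is 5%.

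**The case against.** The strongest defence is that the T0-T2 analysis is valid as it stands, the sample size reproduces, and a statistical analysis plan that is not shown may deal with T3. The first two parts stand, and they limit the severity. The third does not remove the point: section 6 fixes the list of time points, so a plan that added T3 would contradict the protocol.

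Four stronger readings are tempting and are not supported.

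- *T0-T0 spoils the analysis, or dilutes the group effect to two thirds.* The averaged estimate is rescaled, but step 5 shows that neither F changes. The main-effect F does differ between raw scores and changes (6.21 against 8.65 in the same data), but that comes from subtracting baseline, not from the zero level. The gate in section 6 is the interaction in any case.
- *PASS would never be collected.* Section 7.1.1 omits it, but that section describes monitoring roles. Section 5.2 names PASS as an outcome, and section 5 schedules assessments in general terms. Its visits need reconciling; its collection is not cancelled.
- *The trial could say nothing on durability.* T3 data would exist and could be reported, but as an unplanned analysis.
- *T2 is already the primary time point.* No section says so.

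**Conclusion.** The contradiction is real and concerns the primary outcome: FMA-LE and MBI are scheduled at T3, and section 6 ends at T2. Its effect is confined to T3. One of the three post-baseline visits for these scales, in up to 60 patients, has no planned efficacy analysis, and an effect appearing only there is found at the 5% false-positive rate.

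The contrast of about 5% with about 99% rests on 16 evaluable per group, SD 2.5, a 3-point effect and an assumed equal correlation of 0.6; the higher figure is 92% at 0.4. An effect confined to T3 is an extreme case, chosen to show what the stated test cannot see. The persisting and fading cases in step 4 are closer to the practical question, and there the stated test gives the same answer to both.

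This should be fixed before the data are analysed. It does not undermine the T0-T2 test or the sample size.

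**What to change.** 1. In section 6, for FMA-LE and MBI, make the levels of the time factor T0, T1, T2 and T3 (equivalently T0-T0, T1-T0, T2-T0 and T3-T0). Keep T0 to T2 for the fNIRS, gait, EEG, sEMG and MEP measures.
2. Reconcile sections 5 and 7.1.1 so that each measure has one stated list of visits, including PASS. If PASS is taken at T3, analyse it as in item 1.
3. Name the primary time point for FMA-LE and label the other visits secondary. State the group comparison of T3-T0 explicitly, since the overall interaction alone does not answer the durability question.
4. Do not drop the baseline level while the interaction remains the gate. If T0 is to be a covariate instead, replace the gate by baseline-adjusted group contrasts at the named visits.

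The T3 assessment is already planned, so the cost is wording in sections 5, 6 and 7.1.1, slightly more analysis and one more time level. With 20 per group the interaction degrees of freedom go from (2 × 2, 57 × 2) = (4, 114) to (2 × 3, 57 × 3) = (6, 171).
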